**Methods:**

Forty-five individuals with chronic spinal cord injury are receiving 40 sessions of robotic gait training primed with 30 Hz transspinal stimulation at the Thoracic 10 vertebral level. Participants are randomized to receive 30 min of active or sham transspinal stimulation during standing or active transspinal stimulation while supine followed by 30 min of robotic gait training. Over the course of locomotor training, the body weight support, treadmill speed, and leg guidance force are adjusted as needed for each participant based on absence of knee buckling during the stance phase and toe dragging during the swing phase. At baseline and after completion of all therapeutic sessions, neurophysiological recordings registering corticospinal and spinal neural excitability changes along with clinical assessment measures of standing and walking, and autonomic function via questionnaires regarding bowel, bladder, and sexual function are taken.

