### Trial design {8}

This is a mechanistic, sham-controlled, randomized, parallel design, multi-site (2 sites), clinical trial in which participants with chronic SCI are assigned in equal ratios to one of three study groups (or arms). Group 1: Active transspinal stimulation while standing followed by locomotor training; Group 2: Active transspinal stimulation while lying supine followed by locomotor training; and Group 3: Sham transspinal stimulation while standing followed by locomotor training. Study outcomes are assessed for superiority before (baseline) and after 40 sessions of primed locomotor training.

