### Criteria for discontinuing or modifying allocated interventions {11b}

Interventions are discontinued when unanticipated or serious adverse events (UAEs, SAEs) result from the intervention and call into question the safety of the intervention or if any new information that becomes available during the trial necessitates stopping the trial. The criteria for halting a training session or an experiment include subject complaints of shortness of breath, light-headedness, confusion, severe headache, or dyspnea; onset of angina; excessive blood pressure (BP) changes (systolic BP greater than 200 mm Hg, diastolic BP greater than 110 mm Hg, systolic BP less than 80 mm Hg); inappropriate bradycardia (drop in heart rate (HR) greater than 15 beats per min); increased HR exceeding 80% of the predicted maximum HR (HRmax = 220 − age); or participant reports a Borg perceived exertion rate of greater than 15. Should the session be halted, the participant will be asked to rest while BP and HR are monitored and will resume only when BP and HR return to baseline values. If any of these conditions persist after rest, the participant’s primary physician will be contacted, and the participant is referred for evaluation. If the participant complains of angina at rest, loss of consciousness occurs, or cardiac arrest, 911 will be called immediately. There are no special criteria for modifying allocated interventions.

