### Outcomes {12}

#### Primary outcomes

The primary outcomes are neurophysiological biomarkers that accurately probe corticospinal and spinal neuroplasticity (at presynaptic and postsynaptic motoneuron levels):Corticospinal neuronal excitability:

We establish the active MEP threshold that corresponds to the intensity that evokes 10 responses of at least 50 mV following 20 1-ms transcranial magnetic stimulation (TMS) pulses in seated subjects. Then, the soleus MEP recruitment input–output curve is assembled while maintaining small-amplitude contractions. During BWS-assisted stepping, MEPs are recorded at 1.3 times the right soleus MEP active threshold randomly at different phases of the step cycle (divided into 16 equal bins or time windows) based on the signal from the right foot switch. During stepping, MEPs are collected before and after intervention using Lokomat settings matched to the baseline, while an effort is made to record MEPs using Lokomat settings matched to those of the last training session. This establishes changes at matched settings and adaptations during more demanding stepping conditions. MEPs recorded at different stimulation intensities (recruitment curve) are measured as peak-to-peak amplitude and normalized to the soleus maximal M-wave (Mmax) evoked by posterior tibial nerve stimulation to counteract differences in muscle fiber composition across subjects. Stimulation intensities are normalized to the intensity corresponding to the 50% of the MEPmax amplitude, estimated based on the sigmoid function fit to the data. For the participants who have obtainable soleus MEPs at baseline, the main outcomes from this experiment are the MEPmax from the MEP recruitment curves and the MEP amplitude at the mid-stance and mid-swing phases before and after the intervention.2)Spinal neuronal excitability:*2a) Soleus H-reflex rate-dependent (or homosynaptic) depression*: To assess restoration of homosynaptic depression exerted at the synapses between muscle spindle primary Ia afferents and alpha motoneurons, soleus H-reflexes following posterior tibial nerve stimulation at the popliteal fossa with a 1-ms pulse are recorded from seated subjects at different frequencies (1.0, 0.33, 0.2, 0.125, and 0.1 Hz). Homosynaptic depression is greatest at 1.0 Hz and fully recovers at 0.125 and 0.1 Hz [69]. Homosynaptic depression cannot be recorded during stepping because it is abolished by strong spinal inhibitory circuits and efferent activity. The main outcome measure from this neurophysiological biomarker is the soleus H-reflex 1.0/0.1 Hz ratio [70].*2b) Soleus H-reflex depression by antagonistic nerve stimulation*: To examine the restoration of reciprocal inhibitory actions on antagonistic alpha motoneurons, the soleus H-reflex is conditioned by common peroneal nerve (CPN) stimulation at conditioning-test (C-T) intervals of 0, 1, 2, 3 and 4 ms, with subjects seated [71–75]. Reproducible CPN conditioning stimulation is ensured by using a stable, small-amplitude TA M-wave and similar soleus M-wave amplitudes under control and conditioning stimulations. Soleus H-reflexes are measured as peak-to-peak amplitude, accepted for M-waves ranging from 2 to 8% of the maximal M-wave (Mmax), and normalized to the Mmax. The main outcome is the amplitude of the conditioned soleus H-reflex as a percentage of the control H-reflex. The C-T interval for which reciprocal inhibition is present or reciprocal facilitation is the smallest is further investigated during BWS-assisted stepping. The main outcomes are the conditioned H-reflex at rest and during the stance and swing phases of BWS-assisted stepping, which both reflect the amount of reciprocal inhibition.*2c) Control and conditioned soleus H-reflexes during stepping*: During standing with BWS as needed, the soleus H-reflex and M-wave recruitment curves are assembled. Then, each participant steps with the assistance of the Lokomat, and soleus H-reflexes are recorded under control conditions and following CPN conditioning stimulation randomly across 16 equal time bins into which each step cycle is divided based on the signal from the foot switch [75]. The tibial nerve stimulation intensity is adjusted in real-time online to evoke H-reflexes such that their corresponding M-waves are 2–8% of the Mmax evoked 80 ms after the test H-reflex at each bin (Fig. 3). Control and conditioned soleus H-reflexes during stepping are collected before (baseline) and 1–2 days after completion of all 40 intervention sessions at Lokomat settings matched to baseline and the last training session. This approach determines changes at matched settings and reflex adaptation at more demanding settings [76]. During stepping, soleus H-reflexes are measured as peak-to-peak amplitude, accepted for M-waves ranging from 2 to 8% of the Mmax, normalized to the Mmax, and averaged for each bin of the step cycle. The main outcome is the control and conditioned soleus H-reflex amplitude normalized to the Mmax at mid-stance and mid-swing phases.

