The soleus H-reflex amplitude during assisted stepping in 11 persons with motor incomplete SCI (AIS C-D) recorded from the right leg was compared before and after locomotor training [26]. Based on the amplitude of the soleus H-reflex at mid-stance before and after training (difference in means of pre versus post: 13.67, pooled standard deviation: 17.4), the effect size was 0.79. To predict sample size at a power of 0.80 at α = 0.05 using a one-way ANOVA across 3 groups, 21 total subjects are needed. We will enroll 45 subjects, so we will be adequately powered even if subjects drop out at a higher than expected 20% rate.

Limb coordination relies on the strength of reciprocal inhibition between antagonistic muscles. We used data from a study performed by our group that examined short-latency inhibition from ankle flexor afferents onto ankle extensor motoneurons at rest in 13 persons with AIS C-D SCI before and after locomotor training [28]. Based on the amplitude of the conditioned H-reflex at the conditioning-test interval of 2 ms before and after training (difference in mean of pre versus post: 15.04, pooled standard deviation: 17.21), the effect size was 0.874. To predict sample size at a power of 0.80 at α = 0.05 using a one-way ANOVA across 3 groups, 18 total subjects are needed. We will enroll 45 subjects, so we will be adequately powered even if subjects drop out at a higher than expected 20% rate. Please note that the established power was based on data from SCI subjects who received either transspinal stimulation or locomotor training separately and not combined.

*Aim 3*: Determine if priming locomotor training with high-frequency transspinal stimulation improves limb coordination and the ability to stand and walk. These are secondary measures, and the study is not powered based on these outcomes.

Collectively, an average of 6 to 8 subjects per group is needed to establish significant differences for primary outcomes before and after transspinal stimulation or locomotor training. By enrolling 15 participants per group, the study will be robustly over-powered to detect these differences despite a projected possible 20% dropout rate, sporadic missing data values, or lower-than-expected observed effect sizes.

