## Data collection and management

### Plans for assessment and collection of outcomes {18a}

Neurophysiological biomarkers and clinical outcome assessments at baseline and after 40 sessions of therapy are taken by the same investigator while using the same equipment and settings to ensure consistency and repeatability of recordings and assessments. Laboratory tests/experiments involve recordings of muscle action potentials following brain and/or peripheral nerve stimulation via surface EMG electrodes based on consensus standards for electrophysiological recordings. Consistency of recordings between sessions is ensured from using similar anatomical landmarks, detailed notes on thresholds, amplitude, and behavior of action potentials at a wide variety of stimulation intensities. Data from each participant is checked for completeness through validity checks.

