### Plans to promote participant retention and complete follow-up {18b}

Explanation of the study, including possible benefits, increases recruitment and retention in randomized clinical trials [92]. It is a standard procedure in our lab to describe the research study in detail and answer all questions that a participant may have. The eligible participant is always encouraged to ask questions about the procedures and no information is withheld. During the discussion, participants are informed of the expectation that they can commit to traveling to either site for training/intervention sessions at least 4 times per week for up to 3 months. If the participant or study team perceives difficulty in meeting these expectations, then enrollment is deferred. After the consent form is signed, we develop a calendar for each participant based on the time needed to come to the lab, job obligations, or other commitments. The calendar includes all experimental and training sessions for the total duration of the study and is emailed to the participant. We also make use of electronic calendar invitations for reminders, and emails or texts before each visit depending on the participant. These procedures can decrease some common reasons for dropouts in clinical trials such as fear and anxiety during the study, schedule conflicts, forgetting visits, lack of appreciation, and misunderstood expectations. Thus, the procedures that we follow — explaining the importance of participation, setting expectations, reminders of visits, accommodation of the schedule, and promptly responding to inquiries — are expected to contribute to better retention of participants.

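### Post-treatment outcomes are tied to completing 40 sessions and no assessment is stated for participants who stop early, so their primary values would be missing or imputed from completers

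*Protocol article*

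**What the plan says.** The sections that time the post-treatment outcomes agree with one another.

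- Abstract, Methods: "At baseline and after completion of all therapeutic sessions, neurophysiological recordings" are taken.
- Trial design {8}: "Study outcomes are assessed for superiority before (baseline) and after 40 sessions of primed locomotor training".
- Outcomes {12}, item 2c: control and conditioned soleus H-reflexes during stepping are "collected before (baseline) and 1–2 days after completion of all 40 intervention sessions". The 1–2 day window is stated only for this outcome.
- Section {18a}, under data collection, has the same timing: "Neurophysiological biomarkers and clinical outcome assessments at baseline and after 40 sessions of therapy are taken by the same investigator".
- Participant timeline {13}: the final visits t44 and t45 follow intervention visits 4 to 43. The checks at t15 and t30 cover stimulation threshold and locomotor EMG, not the primary biomarkers.

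The article foresees loss. The sample size section calls 45 participants sufficient "despite a projected possible 20% dropout rate", and section {11b} says "Interventions are discontinued when unanticipated or serious adverse events (UAEs, SAEs) result from the intervention" and call its safety into question. Neither place says whether someone who stops is assessed afterwards. The retention section {18b} deals with explanation, scheduling and reminders. Section {20c} says that, above 5% missing values, mean or median replacement, an extra category level and predictive imputation models will be applied.

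**The concern.** The trial promises a superiority comparison between randomised groups. If the only post-treatment measurement is triggered by finishing session 40, who contributes a post-treatment value depends on something that happens after randomisation and that the allocated arm may influence.

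The burdens differ. Two arms stand for 30 minutes, which section {11a} acknowledges may be demanding, while one lies supine. Two arms receive current throughout at 1.2 times threshold, subject to discomfort; sham receives one minute at motor threshold and then a taper to nothing. If those who stop would have changed less, or more, than those who finish, and this differs between arms, the protection given by randomisation is weakened.

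An analysis plan cannot repair this later, because no analysis recovers a value that could have been recorded and was not. The planned two-way mixed ANOVA needs both time points for each person, so the gap has to be handled by exclusion or by imputation.

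**Working it through.** **Inputs.** 45 randomised, 15 per group, 20% dropout (Sample size {14}); 5% missing-data threshold ({20c}). The correlations r below are assumptions.

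**The plan's own figures.** For three groups, α = 0.05 and total N in multiples of 3:

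- One-way ANOVA with the stated effect sizes entered as Cohen's f: 0.87 gives 18 (power 0.855), 0.79 gives 21 (0.854), 0.874 gives 18 (0.858).
- Within-between interaction with f = 0.71/2 = 0.355 and an assumed pre-post correlation of 0.5: 24 (0.833).

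The stated 18, 21, 18 and 24 therefore reproduce. Whether those effect sizes are apt is a separate question. Dividing by 0.8: 18 → 23, 21 → 27, 24 → 30. Taken at face value, dropout does not break the stated sizes. The issue is bias and what is being estimated, not the stated N.

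**How many are affected.** 0.20 × 45 = 9 without a post-treatment primary value; 36 measured, or 12 per arm if loss is even. 9/45 = 20% exceeds 5%, so the imputation rule applies.

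**What mean filling does.** Fill 3 of 15 with the mean of the 12 completers in that arm.

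- The arm mean stays at the completers' mean.
- The sum of squares is unchanged while its divisor goes from 11 to 14: SD ratio = √(11/14) = 0.886.
- SE ratio = 0.886 × √(12/15) = 0.886 × 0.894 = 0.79.

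The standard error is about 21% smaller than the 12 observed values support. The article does not say which mean is meant. With the mean pooled over arms and equal loss, each arm mean is 0.8 × its completers' mean + 0.2 × the common mean, so a contrast between arms becomes 0.8 times the completers' contrast. Either way the filled values come from completers. Predictive models for the post-treatment value would also be fitted to completers.

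**Illustrative bias with no true effect.** Let r be the correlation between the tendency to stay and the change score, and let a fraction p be lost. The completers' mean is shifted by r × φ(z_p)/(1 − p), in SD of change. For p = 0.20, φ(−0.842)/0.80 = 0.280/0.80 = 0.35.

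| Loss pattern | r = 0.3 | r = 0.5 | r = 1 |
|---|---|---|---|
| 20% informative in one arm, random in the other | 0.105 | 0.175 | 0.35 |
| 5/15 against 1/15, both informative | 0.122 | 0.203 | 0.407 |
| 20% in both arms, equally informative | 0 | 0 | 0 |

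**The case against.** The strongest objection is that this rests on silence. The article condenses a fuller protocol, which may contain an early-exit visit. A reader might infer that early stoppers are never measured, but no sentence says so; it is an inference from a schedule written for participants who follow it. That limits the claim. It does not remove it, because the timing rule itself is stated consistently and carries no exception.

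A reader might also infer that the analysis is of completers only. The document does not support that, since section {20c} provides for imputation. What stands is that the imputed values would be derived from completers.

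Nor do the documents support an argument that participants run out of time. The phrase "at least 4 times per week for up to 3 months" is an expectation discussed before enrolment, not a cut-off. Forty sessions at four a week take 40/4 = 10 weeks.

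Arm-dependent loss is not shown. The active and sham standing arms share the standing burden and its breaks, all arms receive the same locomotor training, and intensity is adjusted for discomfort. The discontinuation text in {11b} can also be read as a rule for stopping the intervention or the trial as a whole, so the firmer evidence of expected loss is the 20% allowance, which is itself a planning figure.

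It is tempting to state a percentage overstatement. If 3 of 15 in one active arm stop with no gain and 12 completers gain 0.80 SD, the mean over all 15 is (12 × 0.80)/15 = 0.64 SD, and 0.80/0.64 = 1.25. That assumes zero gain in every stopper and no loss under sham, so it is not an expected size.

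Finally, measuring after the full course is defensible in a trial that calls itself mechanistic. That supports keeping such an analysis, though not as the only randomised comparison.

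**Conclusion.** The point holds in limited form. The post-treatment primary outcomes are anchored to completing 40 sessions, and the article gives no assessment for those who stop. At its own 20% allowance, about 9 of 45 participants would have no post-treatment primary value if the text is followed as written. The comparison would then rest on completers or on values imputed from them, with standard errors at about 0.79 of the completers' under arm-mean filling of 3 of 15.

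Bias requires early stopping that is informative and that differs by arm. This is plausible from the differing burdens but not demonstrated. Its size is illustrative only: 0.105 to 0.35 SD for 20% informative loss in one arm against random loss in the other, over assumed correlations of 0.3 to 1, and zero if loss is equal and equally informative. The change is worth making because it is cheap and because missing measurements cannot be recovered afterwards.

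**What to change.** State that every randomised participant who is willing and able has the t44/t45 battery: 1–2 days after session 40 or, if training stops early, at a prespecified time, whatever the number of sessions received. The date on which session 40 was scheduled would serve, since section {18b} already sets up a calendar of all sessions for each participant after consent. If the full protocol already provides an exit assessment, one sentence saying so settles this part.

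Make all randomised participants, as allocated, the main comparison. Report sessions received and time since the last session by arm. Keep the 40-session completers as the supportive mechanistic analysis.

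The cost is protocol wording and up to about 9 sets of final visits, within the visits already planned for 45 participants. Nine is a ceiling, because some early stoppers will be unable or unwilling to attend. The main estimate will mix partial dose with a longer gap since the last session, so it may be slightly less favourable than one from completers; reporting sessions and gap by arm lets a reader judge this.

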## Statistical methods

### Statistical methods for primary and secondary outcomes {20a}

For each dependent variable (primary and/or secondary outcome), descriptive statistics including frequencies and percentages for categorical variables and means and percentile distributions for continuous variables to examine the distribution of outcomes and describe the study population are performed.

We will group each dependent variable based on the time of testing (before and after the intervention) and the subject group (2 experimental, 1 sham). A two-way mixed analysis of variance (ANOVA) along with Bonferroni post hoc* t-*tests [93] at 2 3 levels (2: time, 3: groups) to test the main and interaction effects among subject groups and time will be performed separately for each outcome. Furthermore, repeated measures analysis of covariance (ANCOVA) will be performed for each outcome separately with gender, age, level of SCI, and clinically evaluated baseline walking function as separate covariates. Outcomes will not be analyzed based on SCI severity because the ISNCSCI scale does not correlate with improvements in walking ability [3], while age is considered one of the predictors of ambulation in SCI [94].

Mixed regression methods and analysis of slope and threshold of correlation will be used to establish the relationship between the ability to stand and walk, quality of life, and changes in primary outcomes (neurophysiological biomarkers). We will use an identity or log link based on the data distribution.

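### At least nine unranked primary outcomes are each tested at 0.05 with no control across them, and neither the Lokomat setting nor the at-rest conditioning-test interval is fixed for the primary test

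*Protocol article*

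**What the plan says.** All of this is in the protocol article.

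Outcomes {12}, Primary outcomes, names the following as main measures:

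- Corticospinal: "the main outcomes from this experiment are the MEPmax from the MEP recruitment curves and the MEP amplitude at the mid-stance and mid-swing phases". That is three.
- Rate-dependent depression: "The main outcome measure from this neurophysiological biomarker is the soleus H-reflex 1.0/0.1 Hz ratio". That is one.
- Reciprocal inhibition: "The main outcomes are the conditioned H-reflex at rest and during the stance and swing phases of BWS-assisted stepping". That is three.
- Reflexes during stepping: "The main outcome is the control and conditioned soleus H-reflex amplitude normalized to the Mmax at mid-stance and mid-swing phases". The two control measures are new; the two conditioned ones overlap with the previous entry.

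Stepping H-reflexes are collected after treatment "at Lokomat settings matched to baseline and the last training session". For stepping MEPs, the baseline-matched setting is planned and the last-session setting is only attempted. The section does not say which setting supplies the value for the primary test.

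The seated conditioned reflex is recorded at five conditioning-test intervals (0 to 4 ms). On what follows, the section says: "The C-T interval for which reciprocal inhibition is present or reciprocal facilitation is the smallest is further investigated during BWS-assisted stepping". It does not say which interval is analysed at rest. Sample size {14} powers the at-rest measure on data "at the conditioning-test interval of 2 ms before and after training".

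Statistical methods {20a} prescribes a two-way mixed ANOVA "to test the main and interaction effects among subject groups and time will be performed separately for each outcome". Bonferroni is attached to the post hoc t-tests of that ANOVA. Sample size {14} uses a two-sided-equivalent F test at 0.05 and power 0.80 for each of four biomarkers, with no division of alpha.

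**The concern.** The Bonferroni step protects the pairwise comparisons inside one ANOVA. It does nothing about running nine ANOVAs on nine measures that all carry the label primary. With no ranking, alpha split or co-primary rule, the article does not say what pattern of results would make the trial positive. A single significant measure could therefore be reported as a primary finding at a true error rate well above 5%.

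Two further choices are left open inside the primary set. A stepping H-reflex has two post-treatment values. The last-session value is taken at settings that training itself has changed, so its contrast with baseline combines altered support and guidance with any neural change. The at-rest conditioned reflex has five candidate intervals and no designated one.

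This matters because Trial design {8} says outcomes are assessed for superiority, and Objectives {7} looks ahead to a new standard of care.

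**Working it through.** **1. The plan's own sample sizes (alpha 0.05, power 0.80, three groups).**

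Aim 2, one-way ANOVA: noncentral F with 2 and N − 3 df, λ = f²N, and the stated d entered as f.

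- Rate-dependent depression, 25.28/28.92 = 0.87: power 0.76 at N = 15 and 0.86 at N = 18. Stated 18, reproduced.
- Stepping H-reflex, 13.67/17.4 = 0.79: power 0.78 at N = 18 and 0.85 at N = 21. Stated 21, reproduced.
- Reciprocal inhibition, 15.04/17.21 = 0.874: power 0.86 at N = 18. Stated 18, reproduced.

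Aim 1, within-between interaction: f = d/2 = 0.71/2 = 0.355, two time points, assumed pre-post correlation 0.5, λ = f²N × 2/(1 − 0.5). Power is 0.77 at N = 21 and 0.83 at N = 24. Stated 24, reproduced.

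Each calculation therefore spends the whole 0.05.

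**2. Count of primary outcomes.**

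3 (MEP) + 1 (ratio) + 3 (conditioned reflex at rest, stance, swing) + 2 (control reflex at mid-stance, mid-swing) = 9. This counts the conditioned stepping measures once. Counted twice, because one entry expresses them as a percentage of control and the other relative to Mmax, the total is 11.

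**3. Chance of at least one false positive, one group-by-time test per outcome.**

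If independent: 1 − 0.95^9 = 0.370. For 11 outcomes, 1 − 0.95^11 = 0.431.

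For correlated outcomes: simulation with 45 participants, three arms and a common correlation r between outcomes. The r values are assumptions; the document gives none.

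| r | 9 outcomes |
|---|---|
| 0 | 37% |
| 0.3 | 33–34% |
| 0.5 | 28% |
| 0.7 | 21–22% |

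Within aims, if independent: Aim 1 has three outcomes, 1 − 0.95^3 = 14%. Aim 2 has six, 1 − 0.95^6 = 26%.

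**4. What raises it.**

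- Four of the nine are stepping H-reflexes with a firm second setting: 9 + 4 = 13 tests, 1 − 0.95^13 = 49% if independent.
- Adding the two stepping MEPs at the second setting gives 15 tests: 54% if independent, about 27% to 47% at r = 0.7 to 0.3.
- Counting the group main effect with the interaction, nine outcomes give about 61% if independent and 38% to 56% at r = 0.7 to 0.3 (pre-post correlation 0.5 assumed).

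**5. Power after a correction.**

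Assumes 36 completers (45 less 20%).

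| Input | α = 0.05 | α = 0.025 | α = 0.05/9 = 0.0056 |
|---|---|---|---|
| Aim 1, f = 0.355 | 0.96 | 0.93 | 0.80 |
| Aim 2, f = 0.87 | 0.996 | 0.99 | 0.96 |
| Aim 2, f = 0.79 | 0.99 | 0.97 | 0.90 |
| Aim 2 with f = d/2 (0.435 and 0.395) | 0.60 and 0.51 | about 0.48 and 0.39 | 0.27 and 0.20 |

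The last row matters because the Aim 2 figures are pre-post standardised differences entered directly as ANOVA f. With f = d/2, the totals at alpha 0.05 would be 54 to 57 and 66, instead of 18 and 21.

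**The case against.** The best defence is that this is a mechanistic trial with a separate directional hypothesis for each biomarker, and that an analysis plan could add an adjustment. Part of that stands: the article states no rule that one significant result makes the trial positive, so such a rule is a reader's inference. But the article does more than stay silent. It fixes separate testing, confines Bonferroni to post hoc tests and powers each biomarker at 0.05. Treating each aim as its own family still leaves 14% and 26% if the outcomes are independent.

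Four stronger readings are tempting and are not supported:

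- *A false positive is more likely than not.* With one interaction test on nine outcomes the risk stays below one half. Most measures come from the same soleus muscle, so independence is probably the upper end.
- *There are fifteen primary tests.* That is an upper count. The second setting is firm only for H-reflexes, and the article gives the two settings different purposes: change at matched settings, and adaptation under greater demand. It also already collects the matched comparison. What remains is that neither setting is named for the primary test.
- *Choosing the interval from seated data biases the results.* The chosen interval is carried into new stepping recordings, so selection noise in the seated values does not enter the stepping baseline. The rule is the same in every arm and does not by itself bias the between-arm test. Nor does the text say that the selected interval is the one analysed at rest.
- *The 2 ms used for sample size contradicts an individual interval during stepping.* It does not; one concerns rest and the other stepping. The gap is only that no interval is designated at rest.

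**Conclusion.** The point holds in this limited form. The article sets out at least nine unranked primary outcomes and a testing scheme that leaves the error rate across them uncontrolled. The chance of at least one false positive is about 37% under independence and about 21% to 34% at correlations of 0.7 to 0.3, against a nominal 5%. These figures assume one group-by-time test per outcome, no true effects and a common correlation that the document does not supply. They rise if both Lokomat settings or the group main effects are also tested.

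The undesignated setting and at-rest interval add avoidable freedom to the primary analysis. They are not shown to bias the comparison between arms. The plan should be changed, but the defect does not invalidate the design.

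**What to change.** Before unblinding, amend the plan as follows.

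- Name one primary outcome per aim and test the two with Holm at an overall 0.05. An example is soleus MEPmax for Aim 1 and the 1.0/0.1 Hz ratio for Aim 2. The alternative is to keep all nine and apply Holm across them.
- If MEPmax is chosen, state that it covers only participants with obtainable soleus MEPs at baseline, so the analysed number may be below 36. Its planning data were tibialis anterior MEPs in healthy subjects.
- Report the remaining outcomes as secondary, with Holm or false-discovery control.
- Make the baseline-matched Lokomat recording the analysis value for every stepping outcome, and label last-session recordings exploratory.
- Analyse the at-rest conditioned H-reflex at 2 ms, as in the sample size.

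No new data are needed. The costs are fewer claims that can be called primary, and a documented amendment with registry alignment in a trial that has recruited since March 2021. There is also a loss of power. On the article's own effect-size inputs the loss is affordable: 36 completers keep at least 0.93 at 0.025 and at least 0.80 at 0.0056. If the Aim 2 inputs are converted as f = d/2, power is already only about 0.51 to 0.60 at 0.05 and falls to about 0.39 to 0.48 at 0.025. The article's claim of being over-powered should therefore not be relied on to absorb the correction.
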